###### RISKS AND DISCOMFORTS

The Most common risks associated with use of ziprasidone that occurred in > 30% of exposed patients, based on placebo-controlled trials, include: somnolence, tremor or involuntary muscle movement. Other risks that occurred in between 5% and 16% of patients receiving ziprasidone were restlessness, nausea, vomiting, rash, and dizziness. During clinical trials, a small percentage (0.4%) of patients experienced seizures with ziprasidone.

Pertinent laboratory monitoring during treatment with ziprasidone include complete blood counts (CBCs) and hepatic enzyme levels. Baseline biochemistry profiles also will be obtained to assure that hepatic enzyme levels are within normal range. Women of childbearing potential will have pregnancy tests at the screening and termination visits to assure they are not pregnant and must use a suitable form of contraception during their participation in the protocol.

Venipuncture in order to monitor serum valproate levels, as well as relevant laboratory parameters, may cause temporary bruising and discomfort to subjects. This risk will be minimized by the use of trained and experienced phlebotomists to perform venipuctures.

Subjects may become upset or feel uncomfortable with questions used in the clinical assessments. This risk will be minimized by allowing subjects to skip and go to the next question if they become uncomfortable.

There is an inherent and unavoidable risk for worsening of the underlying psychiatric condition (either depression or else cycling from depression to mania or mixed mania) due to the natural course of illness and possible lack of efficacy with either active drug or placebo. This risk will be minimized by close, careful and regular monitoring of psychiatric symptoms by research staff throughout the protocol. For subjects whose clinical conditions may worsen, the investigator may deem it appropriate to discontinue the study protocol and arrange for routine care outside of the research study.

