#### Inclusion Criteria

1. Age 18-65
2. Diagnosis of Bipolar Disorder Type II, or unipolar major depressive disorder
3. If female, nonpregnant/nonlactating
4. If a sexually active female of reproductive potential, must be using adequate contraception (i.e., oral contraceptives, barrier protection, or prior tubal ligation)
5. Currently meets DSM-IV criteria for a major depressive episode, and presence of 2 or 3 DSM-IV manic criteria
6. All other baseline psychotropic drugs will be allowed to be continued unchanged. However, if antidepressant use had been initiated in the previous 2 months, or was thought to be contributing to the depressive mixed state, then antidepressant medications would be discontinued 2 weeks (5 weeks for fluoxetine) before initiating the study.
7. Decisional capacity will be assessed by [name] utilizing the standard psychiatric approach to assessing capacity:

- Factual understanding
- Appreciation of available options
- Rational thought process
- Communication of awareness

Please note that the subjects invited to participate are not psychotic, and do not have cognitive impairment.

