### Visit-Specific Treatment and Evaluation Sequence

Visits will be planned to occur at the screening visit and weeks 0, 1, 2, 3, 4, 5, 6. Research scales will be administered at each visit. For a detailed description of which scales are administered per visit, please see “XIV. Study Visit Schedule” on page 21. No research procedures will be performed without a patient first signing an informed consent. Laboratory tests, consisting of CBC with differential, biochemistry profile, ECG and urine pregnancy test, will be conducted prior to the acute phase, prior to the continuation phase, and at study termination. Physical examination and vital signs will be assessed at study entry and termination visits. Patient termination will occur if the patient experiences a worsening of MADRS scores greater than 30% above the baseline score in two successive visits or if MRS > 20 in two successive visits, or based on clinician judgment or patient preference.

1. Concomitant Medication and Therapy

All allowed concomitant medications will be unchanged throughout the study.

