###### STUDY VISIT SCHEDULE

|  | **Screening** | **Weeks** | | | | | | | | | | | | | | | |
| --- | --- | --- | --- | --- | --- | --- | --- | --- | --- | --- | --- | --- | --- | --- | --- | --- | --- |
| **0** | **1** | | | **2** | | | **3** | | | **4** | | | **5** | | **6** |
| **VISITS:** | | | | | | | | | | | | | | | | | |
| Office Visits | • | • | • | | | • | | | • | | | • | | | • | | • |
| **PSYCHOMETRIC SCALES:** | | | | | | | | | | | | | | | | | |
| Demographics Form | • |  | |  | | |  | | |  | | |  | |  | |  |
| SCID Depression & Mania Modules | • |  | |  | | |  | | |  | | |  | |  | |  |
| Montgomery Asberg Depression Rating Scale (MADRS) | • | • | | • | | | • | | | • | | | • | | • | | • |
| Quick Inventory for Depressive Symptoms (QIDS) | • | • | | • | | | • | | | • | | | • | | • | | • |
| Mania Rating Scale (MRS) | • | • | | • | | | • | | | • | | | • | | • | | • |
| Hamilton Scale of Anxiety (HAM-A) |  | • | | • | | | • | | | • | | | • | | • | | • |
| Quality of Life Enjoyment and Satisfaction Questionnaire (Q-LES-Q) |  | • | | • | | | • | | | • | | | • | | • | | • |
| Scale to Assess Unawareness of Mental Disorder (SUMD) |  | • | | • | | | • | | | • | | | • | | • | | • |
| Drug Attitude Inventory (DAI) |  | • | | • | | | • | | | • | | | • | | • | | • |
| Clinical Global Impression Bipolar Depression (CGI-BP) |  | • | | • | | | • | | | • | | | • | | • | | • |
| Global Assessment of Function (GAF) |  | • | | • | | | • | | | • | | | • | | • | | • |
| LIFE-RIFT |  | • | | • | | | • | | | • | | | • | | • | | • |
| Systematic Assessment for Treatment Emergent Events |  | • | | • | | | • | | | • | | | • | | • | | • |
| Barnes Akathisia Scale (BAS) |  | • | | • | | | • | | | • | | | • | | • | | • |
| Simpson-Angus Scale for extrapyramidal symptoms (SAS) |  | • | | • | | | • | | | • | | | • | | • | | • |
| The structured Family History Screen (FHS) |  | • | |  | | |  | | |  | | |  | |  | |  |
| The Temperament and Affective Disorders Questionnaire (TEMPS-A) |  | • | |  | | |  | | |  | | |  | |  | |  |
| Side Effects Checklist |  | • | | • | | | • | | | • | | | • | | • | | • |
| Past Medication Response Structured Assessment |  | • | |  | | |  | | |  | | |  | |  | |  |
| PTSD Scale |  | • | |  | | |  | | |  | | |  | |  | |  |
| **MEDICAL ASSESSMENTS:** | | | | | | | | | | | | | | | | | |
| PE & Vital Signs |  | • | | |  | | |  | | |  | | |  | |  | • |
| Safety Labs | • |  | | |  | | |  | | |  | | |  | |  | • |

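### The only scheduled pre-treatment pregnancy test is at screening; none is required at Week 0, and the interval between the two visits has no stated limit

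*Protocol*

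**What the plan says.** Three parts of the protocol bear on when a woman is tested before treatment.

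- **Risks and Discomforts:** "Women of childbearing potential will have pregnancy tests at the screening and termination visits to assure they are not pregnant". The same sentence adds that these women "must use a suitable form of contraception during their participation in the protocol".
- **Visit-Specific Treatment and Evaluation Sequence:** "Laboratory tests, consisting of CBC with differential, biochemistry profile, ECG and urine pregnancy test, will be conducted prior to the acute phase", with further rounds before a continuation phase and at termination. The visits are listed thus: "Visits will be planned to occur at the screening visit and weeks 0, 1, 2, 3, 4, 5, 6".
- **Study Visit Schedule:** the safety laboratory row is marked at screening and at Week 6 and is blank at Week 0. The row directly above it, "PE & Vital Signs", is marked at Week 0.

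Three inclusion criteria also matter. Item 3 reads "If female, nonpregnant/nonlactating". Item 4 reads "If a sexually active female of reproductive potential, must be using adequate contraception". Item 6 lets other psychotropic drugs continue. If an antidepressant was started in the last 2 months, or is thought to contribute to the mixed state, it adds: "then antidepressant medications would be discontinued 2 weeks (5 weeks for fluoxetine) before initiating the study".

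The protocol states no maximum time from screening to Week 0.

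**The concern.** Eligibility requires that a woman is not pregnant, and the pregnancy test is the protocol's own means of finding a pregnancy that nobody knows about. Its result is obtained at screening, while treatment starts at a later visit with no upper limit on the delay. At Week 0 the investigator can apply inclusion criterion 3 only to a pregnancy that is already known.

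A site that follows the plan exactly could therefore randomise and dose a woman whose pregnancy began after screening, or was too early to show at screening. With 1:1 allocation she has a one-in-two chance of receiving ziprasidone. What is at stake is participant safety and correct application of an eligibility criterion. No estimate, power figure or error rate is affected.

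**Working it through.** The protocol has no figure of its own to reproduce. The check is mainly a comparison of sections, followed by a rough sizing on assumed inputs.

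**1. When is the pre-treatment test?** Risks and Discomforts names the screening visit. The schedule marks the safety laboratory tests at screening and not at Week 0. The visit-sequence section asks only for a test before the acute phase, and a screening test satisfies that. The three places are compatible. Together they require one pre-treatment test, at screening.

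**2. Does the looser wording help?** A test before the acute phase could be done closer to dosing, so a site may add one at Week 0 without departing from that section. Nothing requires it to.

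**3. How old can the result be at first dose?** Week 0 is taken here as the start of dosing. No limit is stated, so the age of the result is unbounded on paper. The washout gives conditional minimum values:

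- washout after screening: at least 2 × 7 = 14 days, or 5 × 7 = 35 days for fluoxetine;
- washout before screening: it adds 0 days.

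The protocol does not say which order applies, or how many patients will need a washout.

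**4. Rough size.** The inputs below are assumptions and are not in the protocol: 50 women of childbearing potential among the 100 planned patients, an annual conception probability r despite contraception of 1% to 10%, and d = 7 to 35 days from screening to Week 0. The 1:1 allocation is from the protocol.

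Expected conceptions in the interval = 50 × [1 − (1 − r)^(d/365)]; multiply by 0.5 for those allocated to ziprasidone.

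| r | d (days) | Expected conceptions | Allocated to ziprasidone |
| --- | --- | --- | --- |
| 1% | 7 | 0.0096 | 0.0048 |
| 5% | 14 | 0.098 | 0.049 |
| 10% | 35 | 0.503 | 0.251 |

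The last row needs the highest conception rate and a 35-day interval for every woman, whereas the 5-week washout applies only to fluoxetine users who must stop. Realistic values lie well below it. The formula counts conceptions after screening only; one shortly before screening and too early to show there would add slightly to the count. In the other direction, a Week 0 urine test would miss a conception of the last few days, so it gains most when the interval is long.

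**The case against.** The strongest reply is that nothing here is stated wrongly. The sections agree, and the risk section read in full sets out a coherent scheme: a test at entry, contraception in between, a test at exit. On that reading contraception is the protocol's chosen cover for the interval, and the text nowhere promises certification at first dose. The expected number of events is very small and rests wholly on assumed inputs. The protocol describes no specific fetal risk from ziprasidone against which to weigh it.

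Most of this stands, and it limits the point to a minor one. What it does not answer is that contraception lowers the chance of a conception but does not detect one, and criterion 3 needs detection.

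A second reply also stands: a Week 0 test does nothing for conceptions during treatment. With the same formula and d = 6 × 7 = 42 days, these number 0.058, 0.29 and 0.60 at r = 1%, 5% and 10%, more than the pre-dose figure in each row of the table. A reader might take the absence of any test between Week 0 and termination as a measure of this gap. It is not: that absence mostly concerns the dosing period, which the proposed test leaves as it is.

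A reader might also infer that the sections contradict each other, or that women go unprotected between screening and first dose. Neither is supported. The looser wording in the visit-sequence section is compatible with a screening test, and contraception is required both at entry and during participation.

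**Conclusion.** The point holds as a minor safety improvement. The plan requires one pre-treatment pregnancy test, at screening; Week 0 is a separate visit without one; and the interval is not capped. The residual risk is a rare, unrecognised conception between screening and first dose, or one too recent for the screening test to show.

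Its size cannot be taken from the protocol. The range of about 0.005 to 0.25 expected cases allocated to ziprasidone depends on the assumed number of women, conception rate and interval. The argument that washout lengthens the interval further depends on screening coming first, which is not stated. The case for change therefore rests on the low cost of the remedy and not on a large expected harm. It would be wrong to read this as a failure of the trial's safety monitoring as a whole, or as something that bears on the validity of its results.

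**What to change.** Add a urine pregnancy test at Week 0, before the first dose, for women of childbearing potential. Mark it in the Study Visit Schedule and state it in Risks and Discomforts. Keep the screening test, so that most ineligible women are identified before any antidepressant is stopped. With a Week 0 test in place, no cap on the screening interval is needed for this purpose.

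The cost is one dipstick per woman at a visit that already takes place, and a small text change. The drawback is an occasional late screen failure, rarely in a woman who has already completed a washout; she would be someone whom criterion 3 already bars. Conceptions during the 6 weeks of dosing remain covered only by the contraception requirement and the termination test.

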###### POTENTIAL BENEFITS

Patients do not pay for the treatments they receive. They will receive reimbursement for travel and parking expenses.

All subjects will be offered the option of an open label courtesy trial of up to 8 weeks of treatment with ziprazidone at no charge upon their study conclusion. Subjects who do not complete the full 6-week double-blind trial will be eligible for free clinical open treatment with ziprazidone for at least 2 months if they complete an initial baseline visit.

###### ETHICAL AND REGULATORY CONSIDERATIONS

### Institutional Committee Approval

The Institutional Review Boards of the participating institutions will need to approve the protocol.

1. Informed Consent

Participation in this study is voluntary and at no cost to the subjects. All subjects to be entered into the study must be thoroughly informed of the details of the study. Prior to participation in this trial, each subject will have an opportunity to ask questions and will sign a written informed consent statement, which must be witnessed. The informed consent will be obtained by study the PI, [name]. The signed consent forms will be filed with the investigator’s copies of the Case Report Forms for each subject. Any subject may voluntarily withdraw from the study at any time without prejudicing treatment.

### Document Storage and Retention

Documents from Tufts Medical Center will be stored at the offices of the Tufts Medical Center Mood Disorders Program at [name].

### Protocol Amendments

Any protocol amendments will be accompanied by IRB approval and appropriate revisions of consent form documents.

### Confidentiality of Data and Subject Records

Subject research charts will only be identifiable by initials and numbers. The forms used during the screening visit or subsequent visits which may contain substance abuse information will be coded and deidentified, and kept secure and locked in the offices of the Mood Disorders Program Principal Investigator and research coordinator. No subjects will be identifiable in any published data produced from this study.

###### ADDITIONAL INFORMATION REGARDING STUDY CONDUCT

### Case Report and Other Forms

All case report and other forms will be contained in the study research chart of each subject.

### Quality Assurance Audits

Charts will be made available as requested to the sponsor, the participating site IRBs, and the FDA or other federal regulatory bodies for quality assurance purposes.

1. Study Discontinuation/Termination

Patients will be discontinued from the study for the following reasons:

1. 30% worsening of MADRS compared to baseline on two successive visits
2. MRS > 20 in two successive visits
3. Worsening of suicidal ideation (SI) as determined by MADRS suicide item  3 in two successive visits.
4. Clinical worsening sufficient to require hospitalization or other medication interventions in the judgment of the treating psychiatrist
5. Patient noncompliance with medications or appointments
6. Patient preference

After study termination, subjects who do well will receive Geodon. Subjects who do not do well will have the option of receiving Geodon. The blind will be broken only if there is a medical emergency.

D. Serious Adverse Event Reporting

For those studies where the principal investigator is required to report serious adverse advents (SAEs) to Pfizer, the investigator must use the enclosed Serious Adverse Event Fax Cover Sheet together with the FDA’s MEDWATCH form FDA 3500A (for mandatory reporting) which can be downloaded at [www.FDA.gov](http://www.FDA.gov/).

Reporting of Serious Adverse Events: Within 24 hours of first awareness of the event (immediately if the event is fatal or life-threatening), Principal Investigator will report to Pfizer by facsimile any Serious Adverse Event (“SAE,” as defined below) that occurs during the SAE reporting period (as defined below) in a Study subject assigned to receive the Pfizer Product (see Section 5, Pfizer Product). Principal Investigator will report such SAEs using an FDA MEDWATCH form and the *Serious Adverse Event Fax Cover Sheet* provided by Pfizer. SAEs should be reported as soon as they are determined to meet the definition, even if complete information is not yet available. SAEs will be reported to the Tufts Medical Center IRB on the same schedule as the study sponsor.

SAE Definition: An SAE is any adverse event, without regard to causality, that is life-threatening or that results in any of the following outcomes: death; in-patient hospitalization or prolongation of existing hospitalization; persistent or significant disability or incapacity; or a congenital anomaly or birth defect. Any other medical event that, in the medical judgment of the Principal Investigator, may jeopardize the subject or may require medical or surgical intervention to prevent one of the outcomes listed above is also considered an SAE. A planned medical or surgical procedure is not, in itself, an SAE.

SAE Reporting Period: The SAEs that are subject to this reporting provision are those that occur from after the first dose of the Pfizer Product through 28 days after discontinuation of the Pfizer Product.

Follow-Up Information: Institution will assist Pfizer in investigating any SAE and will provide any follow-up information reasonably requested by Pfizer.

Regulatory Reporting: Reporting an SAE to Pfizer does not relieve Institution of responsibility for reporting it to the FDA, as required.

E. Publication and Presentation of Results

All data will be recorded, stored, and analyzed by the Duke and Tufts Medical Center sites. The co-PIs are solely responsible for ultimate presentation and publication of data produced by this study. The study enrollment and follow-up should be complete by the end of 2009. Study results will plan to be presented at the American Psychiatric Association meeting of 2009, and any other meetings as feasible. Publication of the main final manuscript will be planned for 2009. It is expected that two to three other manuscripts assessing secondary outcome measures will also be published by 2009.

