#### Exclusion Criteria

1. Substance abuse or dependence in the previous month or positive urine drug screen at screening or relapse during study to substance abuse (meeting DSM-IV criteria).
2. Medically unstable as judged by study investigators
3. Lack of capacity to provide informed, written, consent to investigators
4. Previous intolerance to ziprasidone or current use of ziprasidone at study baseline or within 3 months of study entry.
5. Serious suicidality as evidenced by score of 3 or greater on suicide item of MADRS
6. Previous diagnosed cardiac arrhythmias
7. Current psychotic major depressive episode
8. History of potentially lethal suicide attempt

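### The only on-study rule tied to the suicide score needs MADRS suicide item 3 at two consecutive weekly visits, although one such score bars entry as serious suicidality

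*Protocol*

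**What the plan says.** Exclusion criterion 5 of the Protocol bars patients with "Serious suicidality as evidenced by score of 3 or greater on suicide item of MADRS". No repeat rating is asked for.

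After randomization, the list under Study Discontinuation/Termination says which patients will be discontinued. Reason 3 is "Worsening of suicidal ideation (SI) as determined by MADRS suicide item", with a threshold of 3, at two consecutive visits. The comparison sign before the 3 is lost in the text available; I read it as 3 or greater.

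On timing, the section Visit-Specific Treatment and Evaluation Sequence states: "Visits will be planned to occur at the screening visit and weeks 0, 1, 2, 3, 4, 5, 6". The visit schedule has the MADRS rated at every one of these visits.

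Three other provisions allow an earlier stop:
- Reason 4 of the same list: "Clinical worsening sufficient to require hospitalization or other medication interventions in the judgment of the treating psychiatrist".
- The termination sentence in the visit section, which allows termination "based on clinician judgment or patient preference". That sentence also gives thresholds for MADRS total and MRS but does not mention the suicide item.
- Risks and Discomforts: "For subjects whose clinical conditions may worsen, the investigator may deem it appropriate to discontinue the study protocol". It also promises close monitoring of symptoms.

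**The concern.** The protocol uses one item and one number for two purposes and treats them differently. Before randomization, one rating of 3 is serious enough to keep a patient out. On blinded drug or placebo, the same rating has to recur at the following visit before the score-based rule applies, and nothing is required in between. Asking for confirmation makes sense for MADRS total and MRS, where the aim is not to stop on ordinary fluctuation. For suicidality, a confirmation that comes a week later is a weak safeguard.

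All patients have a current major depressive episode with 2 or 3 manic criteria, and allocation is 1:1, so half receive placebo. Some will have come off an antidepressant shortly before: where it was started in the previous 2 months or was thought to contribute to the mixed state, "then antidepressant medications would be discontinued 2 weeks (5 weeks for fluoxetine) before initiating the study". During the study, "All allowed concomitant medications will be unchanged throughout the study". While a patient stays in, the drug response is limited to adjusting the dose of blinded study medication. Leaving the study opens the way to open-label ziprasidone or routine care, so the promptness of withdrawal matters.

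**Working it through.** The plan gives no figure on this point to reproduce. The check compares the rules, counts visit patterns, and illustrates the cost of the fix under assumed rates.

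**1. The rules compared**

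| | Entry (exclusion 5) | On study (reason 3) |
| --- | --- | --- |
| Item | MADRS suicide item | MADRS suicide item |
| Threshold | 3 or greater | 3 (sign lost) |
| Ratings needed | 1 | 2, at consecutive visits |
| Required action after one such rating | Exclusion | None stated |

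If the lost sign is "at least" or "equal to", the difference is the repeat requirement. If it is "greater than", the on-study rule is weaker still. The point holds under each reading.

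**2. Delay under the score-based rule.** Ratings on treatment fall at weeks 1 to 6. From a first score of 3 or more to a stop under reason 3 takes one visit interval, nominally 7 days. If the first such score is at week 1, the earliest stop is week 2.

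**3. Patterns that never meet the rule.** Six on-treatment visits give 2^6 − 1 = 63 patterns with at least one score of 3 or more. Those with no two adjacent such visits number:
- one visit: 6
- two non-adjacent visits: C(5,2) = 10
- three non-adjacent visits: C(4,3) = 4, namely weeks {1,3,5}, {1,3,6}, {1,4,6} and {2,4,6}

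The total is 6 + 10 + 4 = 20 of 63. One of the 20 is a single score at week 6, when blinded treatment ends anyway. The other 19 include at least one such score while treatment is still to come. The patterns are not equally likely, so 20/63 is a count and not a probability.

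**4. Cost of a one-visit trigger (assumed rates).** The protocol gives no rate for this item. Assume that all patients are below 3 at week 0, that a = 0.01 to 0.03 newly reach 3 or more each week, and that a score of 3 or more persists to the next visit with probability b = 0.3 to 0.7.

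First score of 3 or more by week 5, the last visit with treatment still to come: 1 − (1 − a)^5
- a = 0.01: 1 − 0.99^5 = 4.9%
- a = 0.03: 1 − 0.97^5 = 14.1%

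Two-visit rule met by week 5. Let L be the share below 3, H the share at a first high score in a run, and F the share stopped, starting from L = 1, H = F = 0. Each week:
- F_new = F + bH
- H_new = aL
- L_new = (1 − a)L + (1 − b)H

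| a | b | First score by week 5 | Rule met by week 5 | Difference per 100 |
| --- | --- | --- | --- | --- |
| 0.01 | 0.3 | 4.9% | 1.2% | 3.7 |
| 0.01 | 0.7 | 4.9% | 2.8% | 2.1 |
| 0.03 | 0.3 | 14.1% | 3.5% | 10.6 |
| 0.03 | 0.7 | 14.1% | 8.1% | 6.0 |

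If every single score led to withdrawal, there would be about 2 to 11 more early stops per 100 patients. That is a ceiling, because the proposed rule lets the psychiatrist keep a patient in with a documented reason.

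**The case against.** The strongest reply is that reason 3 is a backstop and the real protection lies elsewhere. Reason 4 is equally mandatory, needs no repeat visit, and applies as soon as the psychiatrist judges that hospital care or other medication is required. Clinician judgment and patient preference can end participation at any time. A reader might infer from reason 3 that a suicidal patient has to stay on placebo for a week; the documents do not support that. What stands against the reply is that each of these routes depends on judgment or choice and none is set off by the suicide score. No provision asks for an assessment, a repeat rating or a note after one score of 3 or more, so four sites could handle the same score differently without deviating from the protocol.

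Second, entry and stopping rules serve different purposes, and nothing says that their thresholds must match. That is fair. A reader might call this a contradiction in the protocol, but both rules can be followed as written. It is a design choice that can be improved.

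Third, the risk setting is milder than it may look. Baseline psychotropics continue unchanged in many patients, antidepressants are withdrawn only in the defined cases, and psychotic episodes and past potentially lethal attempts are excluded. Also, the schedule sets nominal visit days, and an earlier unscheduled visit is not forbidden. All of this stands and limits the severity.

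Fourth, the proposed rule also relies on the psychiatrist. True, but it makes the score start the judgment, on the same day and on record.

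**Conclusion.** The point holds as a modest participant-safety improvement. Followed exactly, the score-based rule tolerates the protocol's own serious level for about a week, or throughout treatment if the high scores are not adjacent (20 of 63 possible patterns, with up to three such visits). Earlier stopping is available through reason 4, clinician judgment and the risks section, which keeps the severity low. This conclusion rests on the text and the weekly schedule and needs no assumed rate.

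Two further inferences are not supported. One is a stated share of suicidal patients whom the rule would miss: the protocol gives no onset or persistence rate, so the modelled figures only indicate the cost of the fix. The other is bias in the primary comparison: nothing here shows one, since the rule applies equally to both blinded arms and discontinued patients stay in the intent-to-treat analysis.

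**What to change.** Replace reason 3 with wording such as: MADRS suicide item of 3 or greater at any visit: same-day assessment by the treating psychiatrist, and discontinuation unless the psychiatrist documents why continuing is safe; discontinuation if the item is still 3 or greater at the next visit. Put the same rule in the termination sentence of the visit section, which now omits the suicide item. Keep the two-visit form for MADRS total and MRS.

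The cost is a wording amendment in two places with IRB approval. The item is already rated at every visit, so no new measurement is needed. The downside is a few more early withdrawals, within the ceiling calculated above.

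### The only SAE reporting period the protocol defines opens after the first dose, so it misses the 2- or 5-week antidepressant discontinuation that eligibility requires of some patients

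*Protocol*

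**What the plan says.** **Reporting period.** The Serious Adverse Event Reporting section (item D under Additional Information Regarding Study Conduct) sets one window: "The SAEs that are subject to this reporting provision are those that occur from after the first dose of the Pfizer Product", running "through 28 days after discontinuation of the Pfizer Product".

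**Who is covered.** The same section asks the investigator to report to the sponsor an event that occurs "in a Study subject assigned to receive the Pfizer Product".

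**IRB and FDA.** On the IRB it says: "SAEs will be reported to the Tufts Medical Center IRB on the same schedule as the study sponsor". On the regulator it says: "Reporting an SAE to Pfizer does not relieve Institution of responsibility for reporting it to the FDA, as required".

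**Discontinuation before the study.** Inclusion Criteria, item 6, sets the trigger, "if antidepressant use had been initiated in the previous 2 months, or was thought to be contributing to the depressive mixed state", and the consequence, "then antidepressant medications would be discontinued 2 weeks (5 weeks for fluoxetine) before initiating the study".

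**Consent.** Visit-Specific Treatment and Evaluation Sequence says: "No research procedures will be performed without a patient first signing an informed consent". It does not say whether stopping an antidepressant in order to qualify counts as such a procedure.

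**Visits.** The Study Visit Schedule lists Screening, then Weeks 0 to 6, with no contact between Screening and Week 0. The Systematic Assessment for Treatment Emergent Events and the Side Effects Checklist both begin at Week 0.

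**The concern.** The protocol asks for a change of treatment before any study drug is given, in patients who have a current major depressive episode and 2 or 3 manic criteria. It treats suicidality as a leading risk in this population: two of the exclusion criteria concern it (the MADRS suicide item and past attempts), and so does one of the reasons for stopping participation. Yet the clock for serious events does not start until after the first dose.

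A patient who is admitted or attempts suicide during the discontinuation may never reach Week 0. Nothing in the protocol then requires a report of that event to the sponsor, and no scheduled assessment records it. The sponsor and the IRBs would have no systematic information on whether the discontinuation requirement is tolerable. That information is hard to reconstruct later, because patients lost before Week 0 leave few study records.

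**Working it through.** The protocol gives no figure to reproduce on this point. The check sets the passages side by side along the time line of a patient who meets the trigger in criterion 6.

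**Step 1: does the interval lie inside the SAE period?**

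| Stage | Source | Inside the SAE period? |
| --- | --- | --- |
| Antidepressant stopped, 2 or 5 weeks before the study | Inclusion Criteria, item 6 | No: before the first dose |
| Week 0 up to the first dose | Study Visit Schedule; SAE Reporting Period | No |
| After the first dose of the sponsor's product, to 28 days after stopping it | SAE Reporting Period | Yes |

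The window extends 28 days beyond the last dose and zero days before the first.

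**Step 2: would moving the start date be enough?** No. Reporting is also tied to subjects assigned to the sponsor's product. A patient still in the discontinuation period has ordinarily not been assigned to either arm, so an earlier start would have no effect for that patient unless this clause changes too.

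**Step 3: is the nature of the event what excludes it?** No. The SAE definition applies regardless of cause and includes hospital admission and life-threatening events. A suicide attempt or psychiatric admission during the discontinuation can meet the definition; it is the window and the assignment clause that leave it out.

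**Step 4: does another passage fill the gap?**
- *Visit schedule:* no visit between Screening and Week 0, and no adverse-event assessment before Week 0. The MADRS at Week 0 helps only for patients who attend it.
- *Study Discontinuation/Termination:* the rules on MADRS, MRS and the suicide item each need two successive visits. The rule on worsening that needs hospitalisation does not, but it governs leaving the study and is silent on reporting.
- *Risks and Discomforts:* relies on regular symptom monitoring to limit the risk of psychiatric worsening. The schedule provides none in this interval, and the section does not list stopping an antidepressant among the risks.
- *FDA sentence:* preserves a duty, but sets no start date and no collection rule.

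**Step 5: size.** Take the start of the study in criterion 6 to mean Week 0 or the first dose.
- Uncovered time per affected patient: at least 2 × 7 = 14 days, or 5 × 7 = 35 days for fluoxetine.
- Relative to the 6 × 7 = 42 days of double-blind treatment: 14/42 = 33%; 35/42 = 83%.
- The protocol does not say how many patients are affected. With n affected, the uncovered time is between 2n patient-weeks (none on fluoxetine) and 5n (all on fluoxetine). If n were 20 to 40 of the 100 planned (an assumption with no source in the protocol), the range is 20 × 2 = 40 to 40 × 5 = 200 patient-weeks. Double-blind treatment gives at most 100 × 6 = 600. The upper end requires all 40 to have been taking fluoxetine.

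No event rate is given, so no expected number of missed SAEs can be calculated.

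**The case against.** The case on the other side has several parts.

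- **The limit applies to one provision.** A reader might infer that serious events during the discontinuation are never reportable to anyone. The text does not support that. The first-dose limit belongs to the report to the sponsor; FDA reporting is kept separately with no such limit. This stands, although that sentence does not say when collection begins.
- **The IRB sentence may concern timing only.** The schedule it refers to can be read as the 24-hour or immediate deadline, in which case earlier events are not excluded. It also names one IRB in a four-site trial, and the other IRBs' own rules are not in the protocol. This stands. The sentence nevertheless provides no earlier start.
- **The discontinuation may not be study time.** Criterion 6 places it before the study begins, and the protocol does not say that consent comes first. One of the two triggers is a clinical judgement that could be made in ordinary care. It is fair that the sequence is unsettled, but this does not remove the problem. The other trigger, a recent start of the drug, is a fixed eligibility rule, so stopping for that reason is driven by the protocol. If consent comes first, a consented subject is uncovered; if it does not, treatment is changed in order to qualify before consent is given.
- **No trial result changes.** A reader might infer that the reported safety of ziprasidone would look too favourable. That does not follow. These events precede the first dose and, as far as the protocol shows, randomisation, so they cannot bias the comparison of arms. This stands in full.

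**Conclusion.** The concern holds as a gap in safety oversight. The protocol's single defined SAE reporting period starts after the first dose and is confined to subjects assigned to the sponsor's product. It therefore leaves out the antidepressant discontinuation that the protocol requires of some patients, and the visit schedule does not make up for it. The gap is at least 14 days per affected patient, or 35 days for fluoxetine, taking the start of the study to mean Week 0 or the first dose. The finding does not depend on the number affected, which is unknown.

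The conclusion goes no further. It does not say that such events escape every reporting duty, that the IRBs are expressly excluded, or that any efficacy or safety comparison is distorted. It takes no position on the discontinuation rule or its length. It should be settled before enrolment, because events in patients who leave before Week 0 cannot be reliably recovered afterwards.

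**What to change.** Reconcile Inclusion Criteria item 6, Visit-Specific Treatment and Evaluation Sequence, and Serious Adverse Event Reporting as follows:

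1. Start SAE collection, and reporting to the sponsor, at signed informed consent. The existing end of the window can stay.
2. State that consent precedes any antidepressant discontinuation made in order to qualify.
3. Replace the restriction to an event "in a Study subject assigned to receive the Pfizer Product" with all consented subjects, and say explicitly that this includes those who leave before Week 0. Without this change, item 1 has no effect on the discontinuation period.
4. Apply the same start to the IRBs of all participating sites.

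The cost is protocol wording and a few additional SAE forms, some of them for events unrelated to study drug. No visit, patient or analysis is added.
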